# Comparison of Spontaneous Pushing and Directed Pushing During the Second Stage of Labor Among Chinese Women Without Epidural Analgesia: Protocol for a Noninferior Feasibility Study

**DOI:** 10.2196/55701

**Published:** 2024-03-26

**Keywords:** spontaneous pushing, directed pushing, labour stage, labour, labor, obstetric, obstetrics, child, birth, delivery, second, feasibility study, China, Chinese, women, protocol, maternal-neonatal outcomes, maternal, healthcare, labouring women, cohort, effectiveness, Midwives, midwife, midwifery, childbirth

## Abstract

**Background:**

Maternal pushing during the second stage of labor could influence labor progress and maternal-neonatal outcomes. Although the image of health care providers directing the laboring women to push during the second stage of labor could be commonly observed globally, this practice is not sufficiently researched and is questioned regarding its effectiveness and outcomes on the mother and baby. Meanwhile, a strategy referred to as “spontaneous pushing,” which supports women to push by following their bodily urges, has been evaluated in several trials. However, in China, spontaneous pushing is not common practice. Notwithstanding the evaluation of spontaneous pushing, there is a lack of high-quality evidence to support either strategies of directed pushing or spontaneous pushing.

**Objective:**

This study aims to test the feasibility of a future randomized controlled trial to compare the effects of spontaneous pushing and directed pushing during the second stage of labor for maternal and neonatal outcomes in China.

**Methods:**

A nonrandomized, single-group, noninferiority feasibility study will be conducted in a public hospital in Hebei Province, China. In total, 105 women meeting the selection criteria will be recruited to receive the intervention (spontaneous pushing), while 105 sets of medical notes from women who received routine care (directed pushing) will be identified and reviewed to compare outcomes for both cohorts. A mixed methods approach will be used to assess primary outcomes (feasibility and acceptability) and secondary outcomes (effectiveness).

**Results:**

Data collection took place between May and October 2023. A total of 110 women were invited to participate in the intervention of spontaneous pushing. Midwives’ interviews were conducted and will be transcribed for analysis in March 2024. The data analysis is planned to be completed by May 2024.

**Conclusions:**

This feasibility study will provide important information by conducting a full-scale clinical trial in the future as well as the potential facilitators and barriers of it. A future randomized controlled trial is likely to have considerable policy and funding impacts regarding pushing management during the second stage of labor and improvement in women’s childbirth experience.

**Trial Registration:**

Chinese Clinical Trial Register ChiCTR2300071178; https://tinyurl.com/mudtnbft

**International Registered Report Identifier (IRRID):**

DERR1-10.2196/55701

## Introduction

### Background

To achieve physiological childbirth, it is acknowledged that sound maternity practice should aim primarily at giving every woman an opportunity to achieve normality if that is what women choose [1]. More recently, a clinical practice that supports a woman to follow their bodily desire to push during the second stage of labor has been evaluated in several clinical trials [2-5]. This practice is called “spontaneous pushing.” However, this is not a new practice; rather, it is a return to previous practice because it is believed that women in the past gave birth unaided. During spontaneous pushing, a woman takes several breaths in between pushes and is encouraged to give several short pushes throughout the duration of 1 uterine contraction [6]. This could occur with open and closed glottis, depending on women’s preference [6]. Evidence from a systematic review confirmed that spontaneous pushing did not necessarily lead to a longer duration of the second stage of labor [7]. In addition, women in the spontaneous pushing group are less likely to experience an extended episiotomy and cesarean birth during labor [8].

Meanwhile, in most hospital settings around the world, directing a woman to push during labor is commonly observed [7]. This is usually called “directed pushing.” In this context, women are required to follow specific instructions from health care providers and to push in the Valsalva maneuver, involving taking deep breaths and pushing long and hard with closed glottis [7]. At the beginning of the last century in resource-rich countries, promoters of natural birth introduced and advocated this way of directed pushing [9]. They believed that directed pushing could expedite the second stage of labor and avoid the use of forceps, which was commonly used at that time [10]. However, subsequent findings revealed that directed pushing unfavorably alters maternal physiology and contributes to adverse fetal outcomes [11], including poor fetal acid-base balance [12], fetal heart rate increase or decrease [13], low umbilical cord pH and partial pressure of oxygen levels [14], low Apgar scores at 1 and 5 minutes [12], and decreased cerebral oxygenation [15].

Effective spontaneous pushing during the second stage of labor contributes to satisfactory labor progress and improved maternal and neonatal outcomes. The World Health Organization [16] recommends that women in the expulsive phase of the second stage of labor should be encouraged and supported to push spontaneously. Both the Association of Women’s Health, Obstetric and Neonatal Nurses and the American College of Nurse-Midwives advocate the use of spontaneous pushing as best practice, which is consistent with physiological birth practices and evidence improved outcomes [17,18]. In a Chinese context, spontaneous pushing has been recommended by a national guideline by the China Maternal and Child Health Association titled *Clinical Practice Guideline for Normal Birth*. The guideline recommends that “women are ‘allowed’ to push (spontaneously) during a uterine contraction” [19]. Despite the guideline, the routine practice of directed pushing remains in China. Spontaneous pushing is only conducted in an extremely small proportion of hospitals [20]. More evidence is needed to narrow down the gaps between practice guidelines with clinical routine practice. Consequently, high-quality original trials are required to further explore the evidence on pushing management and outcomes in the Chinese context.

### Aims

As this study will involve a change of practice in the Chinese context, it is ethically required to conduct a feasibility study before a full-scale randomized controlled trial (RCT) can be performed. Additionally, this study will be conducted as part of a PhD candidature; hence, there are time constraints. This study aims to test the feasibility of a future RCT to compare the effects of spontaneous pushing and directed pushing during the second stage of labor for maternal and neonatal outcomes.

This study will include (1) the preparation program for midwives and (2) the implementation of spontaneous pushing during the second stage of labor for women and a comparison with normal standard care (directed pushing).

### Objectives

The primary objective is to test the feasibility of a future RCT to compare the effects of spontaneous pushing and directed pushing for maternal and neonatal outcomes. The secondary objective is to explore the effectiveness of spontaneous pushing and directed pushing for women without an epidural during the second stage of labor.

## Methods

### Study Design

This feasibility study is a nonrandomized, single-group, noninferiority trial. All participants will receive the intervention (spontaneous pushing). A mixed methods approach will be used to assess the primary and secondary outcomes. This protocol adheres to the SPIRIT (Standard Protocol Items: Recommendations for Intervention Trials) guidelines (Multimedia Appendix 1) [21].

Table 1 illustrates the objectives, outcomes, and the corresponding study design. Tables 2 and 3 illustrate the chart of the study designs, visits, and assessments for both women and midwives. The flow diagram (Multimedia Appendix 2) demonstrates the enrollment, allocation, follow-up, and assessment process for women to compare the effectiveness of the intervention.

**Table 1 table1:** Objectives, outcomes, and study design.

Objectives and outcomes		Study design
**Primary objective: To test the feasibility of a future RCT^a^ to compare the effects of spontaneous pushing and directed pushing for maternal and neonatal outcomes**		
	Feasibility: recruitment rates, retention rates, and attendance rates of participants	Quantitative study design
	Acceptability: women’s and midwives’ perspectives and acceptability of the intervention	Quantitative study design (survey for women) and qualitative design (interviews for midwives)
**Secondary objective: To explore the effectiveness of spontaneous pushing and directed pushing for women without an epidural during the second stage of labor**		
	Maternal and neonatal outcomes	Quantitative study design

^a^RCT: randomized controlled trial.

**Table 2 table2:** Chart of the study design, visits, and assessment for women.

Time point			Visit 1: during late pregnancy at clinics		Visit 2: at clinics or admission to the prenatal ward		Visit 3: during the second stage of labor		Visit 4: within 2 hours after birth		Visit 5: during the stay in the postnatal ward
**Recruitment**											
	Eligibility screening	✓		✓							
	Informed consent	✓		✓							
**Intervention**											
	Spontaneous pushing					✓					
**Assessment**											
	Case report forms							✓			
	Survey for women									✓	

**Table 3 table3:** Chart of the study design, visits, and assessment for midwives.

Time point			Visit 1: before the preparation program		Visit 2: during the preparation program		Visit 3: during women’s labor		Visit 4: at the end of the study
**Recruitment**									
	Eligibility screening	✓							
	Informed consent	✓							
**Intervention**									
	Preparation program for midwives			✓					
	Support women’s spontaneous pushing					✓			
**Assessment**									
	Focus group interview for midwives							✓	

### Sample Size Determination

One of the objectives of the feasibility study is to gain estimates for a sample size calculation in a future RCT [22]. Although a formal sample size calculation is not necessarily needed in a feasibility study, the sample size was calculated based on the duration of the second stage of labor as a parameter outcome in previous studies. Statistical power analysis was used to estimate sample size in PASS (version 15.0; NCSS LLC, USA) software with statistical power at 90%, α at .05, and dropout rate at 20%. The sample size was calculated to be 105 in each group. Based on clinical judgment and the number of laboring women eligible in the site-specific hospital, a sample size of 105 is set for each group.

To cover all 4 shifts of the roster, a total of 6 midwives will be recruited to deliver the intervention. All the midwives recruited to the study will be interviewed at the end of the study to assess midwives’ acceptability and experience participating in the study.

### Setting

This study will be conducted in a single Birth Centre in the Fourth Hospital of Shijiazhuang, Hebei Province, China. The economic status of the population and the medical resources of Hebei Province is at the average level among all the provinces in China [23], with an annual live birth rate of 762,376 in 2019 [24]. The chosen hospital has one of the largest numbers of annual birth rates in Hebei Province with around 15,600 births in 2022. The default pushing strategy at this hospital is directed pushing, which also aligns with most other hospitals in China.

### Participants

All participants will be recruited from the Fourth Hospital of Shijiazhuang, Hebei Province, China. In total, 105 women will be recruited to receive the intervention. At the same time, 105 sets of medical notes will be identified, and relevant information will be extracted to compare health outcomes between the 2 cohorts. These medical notes will be from women who received standard care, that is, “directed pushing” during the second stage and met the same selection criteria as the women in the spontaneous pushing group. The women whose notes will be reviewed will not be recruited into this study, but permission has been obtained from the site-specific hospital to examine the deidentified medical notes. The demographic data, that is, age and the parity and labor care section of the medical notes will be reviewed and examined and parity in 2 cohorts will be matched for further comparison.

Six midwives will be recruited to support spontaneous pushing. They will be rostered to cover all 4 shifts of the roster to ensure that every recruited woman will be supported to push spontaneously by a recruited and trained midwife. All recruited midwives will be interviewed for the qualitative study part.

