### Data Analysis

The data in this study include both quantitative and qualitative data. For quantitative data, “intention-to-treat” analysis will be used. Statistical description will be conducted by the description of mean value, SD, number of cases, and percentage. Pearson chi-square test will be conducted for categorical variables. Independent group 2-tailed *t* test will be conducted for continuous variables. The threshold for statistical significance will be set at .05. For qualitative data, a framework method will be used, which is commonly applied for the thematic analysis of interview transcripts [30]. After a verbatim transcription of the audio recording, the framework method will help to create and apply an analytic framework in the data analysis process in 5 steps (data familiarization, framework identification, indexing, charting, mapping, and interpretation) [31]. The quantitative and qualitative data will be combined in order to compile recommendations from the feasibility in order to conduct a future RCT.

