## Discussion

### Principal Findings

This is a protocol for a study assessing the feasibility, acceptability, and effectiveness of spontaneous pushing during the second stage of labor among Chinese women without epidural analgesia.

A challenge for this study may likely be the recruitment of laboring women. One of the exclusion criteria for women in this study is “administered epidural analgesia” (Table 3). A large proportion of recruited women may be excluded due to the use of epidural analgesia during labor. The epidural analgesia rate varies from one hospital to another in China [32]. However, the most recently noted rate within the study hospital was around 65% for primiparous women. Despite the anticipated high loss rate of laboring women, this exclusion criterion is set based on the underpinning midwifery philosophy that labor and birth under the use of epidural analgesia is not considered a physiological process. The International Confederation of Midwives [33] states that “Normal birth is where the woman commences, continues and completes labour with the infant being born spontaneously, in the vertex position at term, without any surgical, medical, or pharmaceutical intervention.” The use of epidural analgesia inhibits nerve conduction by blocking painful impulses from the nerves [34]. Although epidural analgesia is considered to be an effective way of pain relief in labor and birth [35], blocking of pain impulses also blocks other impulses conducted by the nerves, including pushing or bearing down urges. At the same time, the “intervention” in this study, spontaneous pushing, encourages laboring woman to feel their bodily urges and push in their most effective way. From this perspective, women who used epidural analgesia during labor may have difficulty feeling their pushing instinct, and hence, they are excluded from this study. The criteria of excluding women who used epidural during labor does not mean to influence women’s choices for their pain relief methods. The reasons for this criteria item will be explained beforehand to women to avoid their potential shame of the use of epidural analgesia during labor.

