### Strengths and Limitations

A strength of this study is the mixed methods that will be used to measure outcome assessment, including quantitative data for effectiveness outcomes and focus group data for acceptability and feasibility outcomes. Another strength of the protocol is that a detailed preparation program for midwives is developed to support spontaneous pushing during labor. A potential limitation of the study is that participants will be both primiparous and multiparous women as we assume that a larger proportion of primiparous women will use epidural analgesia during labor, which will exclude them during the study. Another limitation of the study will be the risk that crossover in clinical context may occur where midwives may facilitate spontaneous pushing when taking care of women from routine practice groups.

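### Nonrandomised, parity-matched cohorts are to be compared with unadjusted t and chi-square tests that use neither the matching nor the recorded age

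*Protocol article*

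**What the plan says.** Study Design states: "This feasibility study is a nonrandomized, single-group, noninferiority trial". The comparator is built from records (Participants): "105 sets of medical notes will be identified, and relevant information will be extracted to compare health outcomes between the 2 cohorts". The same section describes what is taken from the notes, "The demographic data, that is, age and the parity and labor care section of the medical notes will be reviewed", and gives the only design measure against confounding beyond shared eligibility criteria: "parity in 2 cohorts will be matched for further comparison". It does not say whether matching is individual or by frequency, or whether it refers to the women recruited or the women analysed.

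Data Analysis then fixes the tests: "Pearson chi-square test will be conducted for categorical variables. Independent group 2-tailed" t test for continuous variables, at a threshold of .05. It names no covariate, stratum or matched analysis, and its list of descriptive statistics has means and SDs but no medians. For second-stage duration, Table 5 allows either a mean with SD or a median.

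Parity matters to the authors. Strengths and Limitations says: "A potential limitation of the study is that participants will be both primiparous and multiparous women". Principal Findings says of epidural use, which is an exclusion criterion, that "the most recently noted rate within the study hospital was around 65% for primiparous women".

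**The concern.** A nonrandomised comparison needs its analysis to deal with the factors on which the cohorts may differ. Here one factor is handled by matching and a second is recorded, but the stated tests use neither.

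Three consequences follow.

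- **Matching ignored.** If parity is balanced by design and predicts duration, the independent t test still counts the between-parity variance in its standard error. The interval is too wide and power is lost.
- **Age uncontrolled.** Any age difference between the cohorts that is related to outcome goes straight into the estimate.
- **Parity balance may not last.** If more primiparous than multiparous women drop out because of epidural use, and the notes are not matched to those who remain, parity becomes a confounder that the tests cannot remove.

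At stake are the reading of the exploratory effectiveness results and the estimates that the study hands to the planning of the randomised trial.

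**Working it through.** **Inputs from the protocol.** 105 per group and 20% dropout (Sample Size Determination), so 105 × 0.8 = 84 per group. Independent two-tailed t test at .05 (Data Analysis). The protocol gives no difference, SD or margin for duration, so its figure of 105 cannot be reproduced, and every duration input below is an assumption.

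**Assumed inputs.** Lognormal durations, medians 50 min (primiparous) and 20 min (multiparous), log-SD 0.7, half of each cohort primiparous.

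**Step 1: variance on the minute scale.**
- Mean = median × exp(0.7²/2) = median × 1.278: 63.9 and 25.6 min.
- Within-parity variance = mean² × (exp(0.49) − 1): 2,580 and 413, average about 1,497.
- Between-parity variance = 0.5 × 0.5 × (63.9 − 25.6)² ≈ 367.

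**Step 2: parity balanced, no true effect.**
- Real standard error = √(2 × 1,497/84) = 5.97 min.
- Standard error used by the t test = √(2 × (1,497 + 367)/84) = 6.66 min.
- Ratio 5.97/6.66 = 0.896, so the test in effect uses a critical value of 1.96/0.896 = 2.19, which is a two-sided rejection rate of 2.9%.
- Simulation gives 2.6-2.7%, against about 5% for a parity-adjusted model.

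**Step 3: power for a 35% longer second stage, parity balanced (simulated).**

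| Analysis | Power |
|---|---|
| Raw t test | about 54% |
| Parity-adjusted, minutes | about 63% |
| Parity-adjusted, log scale | about 80% |

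Check of the last row: ln(1.35) = 0.300; SE = 0.7 × √(2/84) = 0.108; 0.300/0.108 = 2.78; 2.78 − 1.96 = 0.82, so power is 79%. The gain from 54% to 63% comes from parity adjustment. The further gain to 80% comes from the log scale.

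**Step 4: a smaller parity difference.** With assumed means of 40 and 25 min, coefficient of variation 0.6, 105 per group and a 25% longer stage, the t test's null rejection is 3.7-4.0%. Power is 70-71% (t test), 74-75% (adjusted) and 83% (adjusted, log scale). If parity is unrelated to duration, nothing is lost by ignoring it.

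**Step 5: parity balance lost, no true effect (inputs of Steps 1-2).**
- 40% versus 60% primiparous: bias = 0.20 × 38.3 = 7.7 min. The t test's standard error is now 6.64, so its critical value is 1.96 × 6.64/5.97 = 2.18 real standard errors. The bias is 7.7/5.97 = 1.28 of them; 2.18 − 1.28 = 0.90, a false-positive rate of about 18%.
- 45% versus 55%: bias = 0.10 × 38.3 = 3.8 min, giving about 6%.
- The parity-adjusted log model stays at about 5% in both cases.

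**Step 6: an unmatched factor such as age.** The protocol gives no age effect, so a range is shown. A bias of 0.1, 0.2 or 0.3 SD of duration at 105 per group equals 0.1/√(2/105) = 0.72, 1.45 or 2.17 standard errors. The false-positive rates are about 11%, 31% and 59%.

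**The case against.** **The stakes are low, and an article condenses.** Effectiveness is a secondary, exploratory objective of a feasibility study, and the primary outcomes are descriptive or qualitative. This stands and limits the weight of the point. It does not remove it: the article does not leave the test open but names one that does not fit its own design.

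**Parity is matched, so it cannot confound.** A reader might infer from the epidural rate that parity confounding is certain to remain. The documents do not support that. The matching sentence reads most naturally as matching the cohorts that are compared, and the notes must meet the same criteria, including no epidural. Sound matching in the analysis set removes most of the problem. Step 5 is therefore conditional, and the shares in it are assumed.

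**If matching works, the t test errs on the safe side.** This stands too. The cost is precision, not excess false positives, and Step 4 shows that it can be small.

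**Skew.** One might say that the t test is invalid because durations are right-skewed. The protocol does not describe the distribution. With lognormal data (coefficient of variation 0.6 to 1.5) and 84-105 per group, the t test's null rejection was 4.4-4.8% in simulation. Skew costs power and ease of interpretation, not validity. Table 5 also allows medians.

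**The SD for the future trial.** One might infer that the SD passed on will be wrong. Sample Size Determination says only that estimates will be obtained. It does not say that a pooled SD will be used, and a pooled SD would suit an unadjusted trial with a similar parity mix.

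**Conclusion.** The point holds in a limited form. The stated tests do not fit a nonrandomised comparison matched on parity alone: they discard the benefit of the matching and leave age without a role.

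With parity balanced and strongly related to duration, the expected cost is a conservative test (about 2-3% instead of 5%) and lower power (about 54%, against 63% adjusted and 80% adjusted on the log scale). These sizes rest on assumed medians of 50 and 20 min, log-SD 0.7 and 84 per group, and they shrink as the parity difference shrinks. Bias from parity arises only if balance is lost between the analysed cohorts: about 6% false positives at 45% versus 55%, about 18% at 40% versus 60%. Bias from age is possible, but its size cannot be judged from the protocol.

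Separately, Table 5 and Data Analysis disagree on whether medians may summarise duration. The change should be made, but the feasibility conclusions do not depend on it.

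**What to change.** - In Data Analysis, replace the unadjusted tests by regression on cohort, parity and age: linear for second-stage duration, preferably on log duration, and logistic regression or standardised risk differences for binary outcomes, with a sparse-data method where events are few. Report 95% confidence intervals.
- Report the within-parity SD of duration beside the pooled SD, so that the future trial's planners can use the one that suits their design.
- Reconcile Table 5 with Data Analysis on medians.

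Age and parity are already extracted, so no new data are needed. The article reports data collection as finished in October 2023 with analysis still to be completed, so at that point the change was still open. Adjusting for parity also protects the comparison whichever set of women the notes were matched to, without reselecting notes. The cost is slightly more analysis work and adjusted estimates that are less simple to present than two means and a p value.
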